The PROCalcitonin-based algorithm for antibiotic use in Acute Pancreatitis (PROCAP) trial tests the hypothesis that a procalcitonin-based algorithm to guide initiation, continuation and discontinuation of antibiotics will lead to reduced antibiotic use in patients with acute pancreatitis without an adverse effect upon outcome.

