### Intervention

The intervention is the use of a procalcitonin-based algorithm to guide antibiotic use. The algorithm is presented in Table 1. A study flowchart is shown in Fig. 1. Patients will be randomised in a 1:1 ratio to receive algorithm-guided or standard care. The randomisation will be stratified by patient admission route (direct or tertiary referral).

**Table 1 Tab1:** Procalcitonin-based algorithm to guide antimicrobial use in acute pancreatitis

Evaluation only after enrolment at time of admission to hospital		
PCT result	< 1.0 μg/L	≥ 1.0 μg/L
		
Recommendation on antibiotic use	Do not start antibiotics Stop antibiotics in patients already on antimicrobial therapy	Antibiotic intervention (follow Trust guidelines for prophylaxis or treatment)
		
Follow-up	If there is clinical concern about infection, re-check PCT after 24 h	Reassess clinical condition and re-check PCT after 48 h
PCT result	< 1.0 μg/L	≥ 1.0 μg/L
Recommendation on antibiotic use	No antibiotics (or stop antibiotics)	Continue antibiotics (or start if not already on antibiotics) (consider change in antibiotics if clinically indicated)
Over-ruling the algorithm	Empiric antibiotic therapy is permitted in patients not allocated by PCT algorithm to receive antibiotic but decision to be made only by ITU consultant or HPB consultant surgeon and documented in case notes	

*HPB* hepato-pancreato-biliary, *ITU* intensive therapy unit, *PCT* procalcitonin

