***Primary outcome measure***

The primary outcome measure will be the binary outcome: whether antibiotic use occurs during the index stay.ii)***Secondary outcome measures***Safety non-inferiority endpoint all-cause mortalityDays of antibiotic use (for antibiotics initiated during the index stay) defined as any day (24-h period) when antibiotics were prescribed on the patient’s drug prescription chart and administeredClinical infections defined according to the Centers for Disease Control [29]New isolates of multiresistant bacteria (*Clostridioides difficile*, vancomycin-resistant enterococcus (VRE), methicillin-resistant *Staphylococcus aureus* (MRSA), carbapenemase-producing enterobacteriaceae (CPE))Incidence of multiresistant organism bacteraemiaInfection of pancreatic necrosis—defined either as a result of fine needle aspiration (FNA), radiological evidence of gas in a peri-pancreatic collection or positive microbiological cultures from surgical or post-mortem specimensUse of radiological, endoscopic or surgical intervention [30]Survival at 90 days; time-to-event (mortality) survival (Kaplan–Maier)Length of inpatient stay (in total and by level of care: critical care levels II/III, ward-based care)Re-admission to hospital within 6 weeks of onset of index episodeEpisode-related mortality and causeQuality of life assessed by the EQ-5D-5L questionnaire, at enrollment, discharge and 90 days [31]Cost analysis (from an NHS perspective, including inpatient resource use)iii)***Measurement of outcomes***

The primary (superiority) outcome measure will be antibiotic use (binary endpoint: yes or no) during the index stay. Antibiotics prescribed before the index admission (from the referring hospital or community) will be recorded at admission but not included in the primary endpoint.

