### Randomisation

Web-based randomisation will be provided by the Clinical Trials Unit of the University of Edinburgh (https://www.ed.ac.uk/usher/edinburgh-clinical-trials). Allocation will be in a ratio of 1:1 to routine or algorithm-guided care. Randomisation will be stratified by disease severity (mild or moderately severe/severe) and admission pathway (whether or not the patient has their index (first) admission with acute pancreatitis to the Manchester Royal Infirmary (direct) or is transferred from another hospital (tertiary transfer)). A random block size of 4, 6 or 8 will be applied to each stratum. Patients allocated to either arm will be identified by a label placed inside and on the front of the case notes with copy labels used for ward folders.

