### Data collection

Data collection will use a case report form (CRF) and include source-verifiable data from patient records, including procalcitonin test findings and the list of primary and secondary endpoints. CRFs will be anonymised and contain no individual patient-identifiable information. Patient-level data will be stored by screening and trial log numbers. Data will be recorded on the timeline of the episode, including time from onset of symptoms to admission, days in baseline hospital for tertiary transfers and delay from admission to enrolment. Patients who are discharged and re-admitted within 6 weeks will be regarded as a re-admission for the same episode of care and treatment will be summated. Patients who are re-admitted will be in the same arm as their original allocation. Re-admission elsewhere will be a specific question sought at follow-up (typically at 6 weeks and 90 days). Patients discharged but subsequently admitted elsewhere within 6 weeks will have their pharmacy charts reviewed wherever possible and antibiotic use summated. The trial process and data collection are designed to be minimally burdensome to patients. Clinically, the 90-day follow-up period will complete the involvement of the patient in the trial.

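### Neither antibiotic endpoint starts at randomisation: in-stay use before enrolment dilutes the primary comparison, and antibiotic days misses the stopping of courses that patients arrive on

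*Protocol article*

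**What the plan says.** In the Protocol article, Outcomes, the primary endpoint is fixed as follows: "The primary (superiority) outcome measure will be antibiotic use (binary endpoint: yes or no) during the index stay". One exclusion is attached: "Antibiotics prescribed before the index admission (from the referring hospital or community) will be recorded at admission but not included in the primary endpoint". The first antibiotic endpoint among the secondary outcomes, days of use, is restricted to antibiotics begun within the index stay. Neither definition mentions randomisation.

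Three other places bear on this:

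- Background states the hypothesis that "a procalcitonin-based algorithm to guide initiation, continuation and discontinuation of antibiotics will lead to reduced antibiotic use". Stopping is thus one of the three things under test.
- Intervention, Table 1, gives the action at the first evaluation when PCT is below threshold. For patients already being treated it reads: "Stop antibiotics in patients already on antimicrobial therapy". The table heads that step "Evaluation only after enrolment at time of admission to hospital".
- Data collection lists among the timeline items "days in baseline hospital for tertiary transfers and delay from admission to enrolment". The protocol therefore expects that admission and enrolment may not coincide.

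**The concern.** Allocation can only affect what happens after it. An outcome window that opens at hospital admission can include events from before randomisation. Those events occur at the same expected rate in both arms, add nothing to the contrast, and make a real effect harder to detect.

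The second issue is what the endpoints can see. Some patients will already be on antibiotics when the first PCT result arrives; Table 1 is written for them. If their course came from the referring hospital or the community, antibiotic days leaves it out by definition. The primary endpoint is a yes/no measure, and its treatment of such a course is either exclusion or an almost automatic yes. At stake are the power of the primary comparison and whether discontinuation, for patients who arrive on treatment, is measured at all.

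**Working it through.** **What each endpoint can register**

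| Where and when the course began | Primary endpoint | Antibiotic days | Is earlier stopping registered? |
|---|---|---|---|
| Study hospital, after randomisation | Yes | Counted | In days only; an avoided start shows in the primary |
| Study hospital, between admission and randomisation | Yes in either arm | Counted, including days before randomisation | In days only |
| Before admission, continued; read as excluded from the primary | Not counted | Not counted | Nowhere |
| Before admission, continued; read as use within the stay | Yes after one in-stay dose | Not counted | Only if no dose is given after admission |

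The last two rows are two readings of the same text. The exclusion speaks of antibiotics prescribed before admission, while the endpoint speaks of use during the stay. The article does not say which governs a course that continues.

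**The plan's own figure**

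Inputs from Sample size: 60% control rate, 20-point absolute change (hence 40%), two-sided 5%, 80% power. The pooled-variance formula, with p̄ the mean of the two rates, is

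n = [1.96·√(2p̄(1−p̄)) + 0.8416·√(p₁(1−p₁)+p₂(1−p₂))]² / (p₁−p₂)²

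= [1.96·√0.50 + 0.8416·√0.48]² / 0.04 = (1.386 + 0.583)² / 0.04 = 96.9, so 97 per arm. The stated figure reproduces exactly.

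Power at n per arm is Φ{[(p₁−p₂)√n − 1.96·√(2p̄(1−p̄))] / √(p₁(1−p₁)+p₂(1−p₂))}. At n = 100 this is Φ[(2.000 − 1.386)/0.693] = Φ(0.886) = 81.2%. The recruitment target of 200 is six patients above the calculated 194.

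**Effect of in-stay use before randomisation**

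Let q be the share of all randomised patients who start an antibiotic at the study hospital before randomisation. Patients who arrive on antibiotics are not part of q. The document does not give q, so a range is shown. Two models bracket what the 60% might mean.

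- *Model A:* 60% is the control rate over the whole stay, and the algorithm cuts the remaining starts by the planned one third (20/60). The difference is (0.60 − q)/3.
- *Model B:* 60% versus 40% holds only among patients not yet exposed. The rates are q + 0.60(1 − q) and q + 0.40(1 − q), so the difference is 0.20(1 − q).

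| q | A: rates | A: power at 100 per arm | A: n per arm for 80% | B: rates | B: power at 100 per arm | B: n per arm for 80% |
|---|---|---|---|---|---|---|
| 0 | 60.0 v 40.0% | 81% | 97 | 60.0 v 40.0% | 81% | 97 |
| 5% | 60.0 v 41.7% | 74% | 116 | 62.0 v 43.0% | 77% | 108 |
| 10% | 60.0 v 43.3% | 66% | 140 | 64.0 v 46.0% | 73% | 119 |
| 20% | 60.0 v 46.7% | 47% | 219 | 68.0 v 52.0% | 64% | 146 |

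Worked case, Model A at q = 10%: difference (0.60 − 0.10)/3 = 0.167; power = Φ[(1.667 − 1.385)/0.697] = Φ(0.404) = 66%.

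If the algorithm nevertheless delivers the full 20 points on the endpoint as written, power stays at 81%. With 60% as the whole-stay rate, that needs a relative cut in the remaining starts of 0.20/(0.60 − q): 36%, 40% and 50% at q = 5%, 10% and 20%, against 33% as planned.

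**The case against.** The strongest reply is that the gap is meant to be short. Table 1 places the first evaluation at admission, and Intervention arm protocol sets baseline PCT on the day of admission, called day 0. Recording "delay from admission to enrolment" shows that a delay can occur, not that it is long or that antibiotics are often started within it. This stands: q may be small, and nothing in the document supports a particular value.

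The direction of the effect is also conservative. Randomisation balances earlier use between the arms in expectation, so it dilutes and cannot by itself produce a false claim of benefit. Randomisation is also stratified by admission route, and Analysis plan adjusts for the stratification factors. That too stands, although adjusting for route does not restore a stop that the endpoint never counted.

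A reader might infer that these endpoints cannot show the algorithm stopping any course. The document does not support that: antibiotic days counts each day of a course begun in the stay, so earlier stopping of such a course is registered.

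A reader might also infer that the window is undefined for transferred patients, because Randomisation separates strata by "whether or not the patient has their index (first) admission with acute pancreatitis to the Manchester Royal Infirmary (direct", which seems to put a transfer's index admission at the referring hospital. This is only a clash of wording. The outcome section expressly places the referring hospital's antibiotics before the index admission, so the start of the endpoint window is clear.

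Lastly, the 60% comes from audit data on admitted patients, and a clock that starts at admission matches it more closely. This is a genuine, small cost of moving the clock.

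**Conclusion.** The point holds in a limited form and should be fixed. Neither antibiotic endpoint is tied to randomisation. In-stay use before enrolment counts as a primary event that allocation cannot alter, and it dilutes the difference toward zero. For courses carried in from elsewhere, antibiotic days does not register stopping. The primary endpoint either excludes such a course or scores it yes after one in-stay dose, and the wording leaves this open.

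The loss of power depends on q, which is not reported, and on what the 60% represents. At 100 per arm it is 81% falling to 74–77% at q = 5%, 66–73% at 10% and 47–64% at 20%. These figures are illustrations and not a finding that the trial is underpowered. Even so, q = 5% takes power below the planned 80% under both models.

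To say that the primary result would be biased in favour of the algorithm, or that discontinuation goes wholly unmeasured, would go beyond the document.

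**What to change.** 1. Antibiotic days: count every day on antibiotics from randomisation, wherever the course began.
2. Primary endpoint: define it as antibiotic use after randomisation, with one pre-specified counting rule, identical in both arms, for a course already running at randomisation.
3. Derive antibiotic status at randomisation from drug charts and enrolment time, and adjust for it in the primary model. The article says that antibiotics prescribed before the index admission are recorded; it does not say that status at randomisation is, so this variable has to be constructed.
4. State that the index stay is the study-hospital stay in which the patient is randomised, and align the stratum description under Randomisation with it.

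The cost is mainly wording in the protocol and analysis plan, plus one derived variable from sources the trial already uses. The downside is that the 60% audit rate describes admitted patients, so under the new definition it should be labelled an assumption. The 97 per arm remains valid if 60% and 40% are taken as rates after randomisation.

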### Sample size

Based on current audit data, 60% of patients admitted with acute pancreatitis receive antibiotics [13]. A 20% absolute change in antibiotic use would be a clinically important difference. This effect of intervention has been observed in other studies evaluating a procalcitonin algorithm to guide antibiotic use [23, 28]. A study with 80% power and 5% significance (two-sided) would require 97 patients in each arm (194 patients in total). The study will aim to recruit 200 patients. Assuming a 3.6% mortality rate based on unit audit data [13], the sample size provides a 6.6% non-inferiority margin for the safety measure of overall mortality, assuming no change in mortality, 80% power and 95% CI (one-sided). Previous randomised trials of the use of a procalcitonin measurement algorithm to guide antibiotic use in a range of clinical settings as well as a Health Technology Assessment have shown no evidence of harm from this intervention [23, 24]. However, as there has been no previous evaluation of procalcitonin in an all-comers population of patients with acute pancreatitis, it is useful to include a secondary safety outcome with mortality being the most important factor. The choice of a 6.6% non-inferiority margin is a pragmatic choice based on the projected sample size and the estimated population mortality rate of 3.6%.

### Consent process

Valid consent will be obtained for all patients. Consent procedures will be governed by the Medicines for Human Use (Clinical Trials) Regulations (2004); Schedule 1, part 5 and by The Medicines for Human Use (Clinical Trials) Amendment (No. 2) Regulations 2006, No. 2984 [32, 33]. Where available, Trust-appointed translator services will be used for those patients who are unable to speak or comprehend English (Additional files 1, 2, 3, 4, 5 and 6).

### Informed consent for patients with capacity

For eligible patients who possess mental capacity, a member of the research team will make the initial approach and provide a verbal overview of the study and what participation will involve. The patient will be provided with a written information sheet and given the opportunity to ask questions. After their questions have been answered, they will have sufficient time to consider participation; if they are willing to take part in the study, they will be asked to sign the consent form.

### Consent procedures for patients who lack capacity

As acute pancreatitis may be severe, causing disruption of a patient’s cognitive state or requiring sedation to facilitate advanced organ support in intensive care, some potential participants will lack capacity to consent for enrolment. Such patients may still be enrolled in this study according to the following procedures. Firstly, a treating clinician who is not part of the study team will assess the competence of a potential participant to consent for research. If lack of capacity to consent is confirmed, then valid consent for enrolment may be obtained from a patient’s legal representative. Ideally, this legal representative will be someone who knows the patient and is able to judge whether the patient would have agreed to enrolment in this study. This personal legal representative would usually be their next of kin or someone with whom they had a significant relationship, and is willing to engage with the consent process on the patient’s behalf. If a personal legal representative is not available, then the patient’s professional legal representative may provide consent instead. This will be an independent treating clinician who is not part of the study team. Where a researcher is also the treating health professional, another member of the research team, independent of any responsibility for the clinical care of that patient, will be asked to make the initial approach and/or seek consent from participants or their legal representative. Patients who recover sufficiently to understand the explanation of the study will be asked to consent to continue with the study procedures as soon as possible or be offered the chance to withdraw. If the patient chooses to withdraw from the study procedures, they will be asked for permission to use their study-related data and for permission to collect and use outcome data. For all participants, written consent forms will be signed; their name filled in and personally dated by the patient or by their legal representative and by the Investigator who conducted the consent discussion. A copy of the signed and dated consent form will be provided to the patient and/or their legal representative and another copy filed in the patient’s medical record.

### Withdrawal of consent

Patients can withdraw consent for participation at any time after enrolment. They do not need to give a reason and their clinical care will be unaffected. Patients allocated to the procalcitonin arm will not continue to undergo PCT monitoring of antibiotic use after withdrawal. Data provided up until the time of withdrawal will be retained for use in analyses.

### Randomisation

Web-based randomisation will be provided by the Clinical Trials Unit of the University of Edinburgh (https://www.ed.ac.uk/usher/edinburgh-clinical-trials). Allocation will be in a ratio of 1:1 to routine or algorithm-guided care. Randomisation will be stratified by disease severity (mild or moderately severe/severe) and admission pathway (whether or not the patient has their index (first) admission with acute pancreatitis to the Manchester Royal Infirmary (direct) or is transferred from another hospital (tertiary transfer)). A random block size of 4, 6 or 8 will be applied to each stratum. Patients allocated to either arm will be identified by a label placed inside and on the front of the case notes with copy labels used for ward folders.

### Data collection

Data collection will use a case report form (CRF) and include source-verifiable data from patient records, including procalcitonin test findings and the list of primary and secondary endpoints. CRFs will be anonymised and contain no individual patient-identifiable information. Patient-level data will be stored by screening and trial log numbers. Data will be recorded on the timeline of the episode, including time from onset of symptoms to admission, days in baseline hospital for tertiary transfers and delay from admission to enrolment. Patients who are discharged and re-admitted within 6 weeks will be regarded as a re-admission for the same episode of care and treatment will be summated. Patients who are re-admitted will be in the same arm as their original allocation. Re-admission elsewhere will be a specific question sought at follow-up (typically at 6 weeks and 90 days). Patients discharged but subsequently admitted elsewhere within 6 weeks will have their pharmacy charts reviewed wherever possible and antibiotic use summated. The trial process and data collection are designed to be minimally burdensome to patients. Clinically, the 90-day follow-up period will complete the involvement of the patient in the trial.

### Data storage and transfer

Paper copies of the CRFs will be stored in a locked cabinet in the Chief Investigator’s office within the Manchester University Foundation Trust. These copies will be stored for 12 months after completion of the trial and then destroyed.

Data will be contemporaneously stored in a password-protected database, allowing ongoing monitoring of data quality and completeness. These data will be stored on a secure desktop computer maintained in the office of the Principal Investigator.

Anonymised data transfer for analysis will be sent electronically only to NHS and university email addresses as anonymised password-protected data.

### Analysis plan

Clinical and economic analysis will follow intention-to-treat principles, as detailed prospectively in a Statistical Analysis Plan. Endpoints will be assessed using an appropriate general linear model adjusted for stratification factors; for the primary endpoint, a general linear regression with logit link will be employed. Missing values will be addressed by multiple imputation, having appropriately explored the missingness mechanism, and in accordance with good practice [34]. Chance baseline imbalances and protocol adherence will be explored within sensitivity analyses.

The trial will determine whether the use of a procalcitonin algorithm reduces antibiotic use during acute pancreatitis. Currently, there is clinical uncertainty about guidelines for reducing antibiotic use in this patient group, since this draws on indirect evidence. Hence, a superiority design has been selected, with a null hypothesis that antibiotic use is unchanged by use of the algorithm.

All-cause mortality in 90 days, re-admission within 6 weeks, adverse events (AEs) and serious adverse events (SAEs) will be reported and compared between the two groups. Length of stay in hospital will be reported and compared using a suitable method (according to its distribution). Other secondary outcomes will be reported using appropriate summary statistics.

Data cleaning and analysis will be provided by the study statistician. Analysis will follow intention-to-treat principles, with patients analysed according to randomisation and irrespective of actual use or compliance with the algorithm. Every effort will be made to retain and include all patients who are part of the trial. Data will be analysed using the latest version of STATA (StataCorp).

Economic analysis will be conducted from an NHS perspective, following similar principles and practices to the analysis of clinical outcomes. Analysis of costs will be limited to hospital activity since these will predominantly determine patient costs during the 90-day period. A within-trial economic analysis will use bootstrapped, adjusted, bivariate regression modelling of costs and quality-adjusted life-years (QALYs), adjusted for baseline scores and stratifying variables [35]. Analyses will be presented as an incremental cost-effectiveness plane, as a cost-effectiveness acceptability curve and by net monetary benefit. An expected value of perfect information (EVPI) analysis will also be provided. Given the timeframe of 6 weeks, discounting of future costs and benefits will not be applied.

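### Antibiotic status before randomisation could be added to the primary logit model, and a standardised risk difference reported beside the odds ratio: a modest improvement, not an error

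*Protocol article*

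**What the plan says.** The Analysis plan section fixes the primary model and its adjustment set: "an appropriate general linear model adjusted for stratification factors; for the primary endpoint, a general linear regression with logit link will be employed". Other baseline information enters only later: "Chance baseline imbalances and protocol adherence will be explored within sensitivity analyses". Detail is deferred to a statistical analysis plan that is not shown. No effect measure is named.

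The Outcomes section defines the endpoint: "The primary (superiority) outcome measure will be antibiotic use (binary endpoint: yes or no) during the index stay". Antibiotics from the referring hospital or the community before the index admission "will be recorded at admission but not included in the primary endpoint".

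The Sample size section works on the absolute scale, from a rate of 60%: "A 20% absolute change in antibiotic use would be a clinically important difference". It gives 97 patients per arm for 80% power at two-sided 5%, with a target of 200.

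**The concern.** A patient's antibiotic status before randomisation is the natural baseline counterpart of the endpoint. Table 1 of the protocol has an explicit recommendation for patients already being treated, so such patients are expected in the trial. Admission pathway will capture part of this information, but not community prescribing or differences among transferred patients. The economic analysis adjusts for baseline scores as well as stratifying variables, whereas the primary clinical analysis adjusts for stratification factors alone.

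There is little spare power: recruiting 200 instead of 194 raises it by about one point. A prognostic covariate that is already being recorded could therefore be useful.

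The second issue is scale. A logit coefficient is a conditional log odds ratio. Going from 60% to 40% is an unadjusted odds ratio of (0.40/0.60)/(0.60/0.40) = 0.44, which cannot be read against a 20-point threshold without converting it to risks.

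**Working it through.** **1. The plan's own figure.** Inputs from the Sample size section: 60% versus 40%, two-sided 5%, 80% power. With pooled variance under the null and no continuity correction:

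n = [1.96·√(2·0.5·0.5) + 0.8416·√(0.24 + 0.24)]² / 0.20² = (1.3859 + 0.5831)² / 0.04 = 96.9, so 97 per arm.

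This matches exactly, so the trial was sized as a test of a difference in proportions. The same formula gives power of 80.0% at 97 per arm and 81.2% at 100 per arm.

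**2. Gain against an unadjusted analysis (an upper guide only).** Let f be the share with prior antibiotics and d the gap in in-stay use between patients with and without them, the same in both arms. Variance falls by the fraction f(1−f)d²/0.24. Both f and d are assumptions.

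- No covariate, 100 per arm, unpooled variance: 0.20/√(0.48/100) − 1.96 = 0.927, power 82.3%.
- f = 0.30, d = 0.30: reduction 0.21·0.09/0.24 = 7.9%; effective sample size 200/0.921 = 217; power 85.3%.
- Full range, f from 0.10 to 0.40 and d from 0 to 0.50 (0.40 at most when f = 0.10): reduction 0-25%, power 82-92%.

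The protocol does not plan an unadjusted analysis, so this is not the relevant comparison.

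**3. Gain beyond the planned adjustment.** The setting was simulated with 200 patients, 4,000 runs per scenario and 1:1 allocation within strata. Marginal rates were 60% and 40%. Severe disease and transfer were each assumed at 40%, with log odds ratios of 1.0 and 0.5. The logit model contained severity and pathway, with or without prior antibiotic status. The share with prior antibiotics was assumed at 10% of direct and 30% of transferred patients, or 20% and 50%.

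| Conditional log odds ratio of prior antibiotics | Variance ratio (with/without) | Power without, risk difference | Power with, risk difference |
|---|---|---|---|
| 0 | 1.00-1.01 | 83.9%, 84.3% | 83.7%, 84.5% |
| 0.7 | 0.98-1.00 | 84.5%, 85.0% | 85.1%, 85.1% |
| 1.4 | 0.92-0.95 | 85.3%, 85.0% | 87.1%, 87.4% |
| 2.1 | 0.84-0.89 | 84.0%, 85.4% | 87.8%, 90.7% |

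For scale, at a log odds ratio of 1.4 and shares of 20%/50%, the standard deviation of the risk difference falls from 0.0665 to 0.0637. The half-width of the 95% CI then goes from 1.96·0.0665 = 13.0 points to 1.96·0.0637 = 12.5 points.

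**4. Effect of the scale alone.** In the stratification-adjusted model, power was 83.5-84.8% for the log odds ratio and 83.9-85.4% for the standardised risk difference. The gap is under 1 point.

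**5. Type I error.** In two null scenarios the covariate-adjusted risk difference test rejected in 5.2% and 5.7% of runs (Monte Carlo standard error √(0.05·0.95/4000) = 0.34 points).

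**6. Unequal association by arm.** Table 1 recommends stopping existing antibiotics at a low PCT, which could weaken the association in the intervention arm. With gaps b0 and b1 in the two arms, the reduction in step 2 becomes f(1−f)(b0+b1)²/0.96. For f = 0.30 and a gap of 0.43 in both arms it is about 16%. With an assumed intervention-arm gap of 0.20 it is 0.21·0.63²/0.96, about 9%.

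**The case against.** The strongest objection is that nothing here is wrong. A logistic model adjusted for stratification factors is standard for a stratified trial with a binary endpoint. Further covariates and the summary measure are commonly settled in the statistical analysis plan, which is cited but not shown. This stands, and it makes the point a suggestion. It does not remove the point, because the article does state a primary adjustment set and that set can be improved.

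Several stronger readings are tempting, and the documents do not support them:

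- A reader might infer that the headline result will be an odds ratio. The article names a link function and no effect measure, and the same model can give a risk difference.
- A reader might infer that covariate choice becomes data-driven. The primary adjustment set is pre-specified, and chance imbalances enter only sensitivity analyses.
- A reader might infer that both changes gain precision. Only the covariate does (steps 3 and 4).
- A reader might take the gain from step 2, against an unadjusted analysis. The planned model already adjusts for stratification factors, and admission pathway probably carries part of the same information.
- A reader might assume that nearly all patients arriving on antibiotics will count as events. Pre-admission prescriptions are kept out of the primary endpoint. If a continued course is not an event, a strong positive association cannot be presumed.

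Nor is the change entirely free. What is recorded is prescribing before admission, and the Data collection section notes a delay from admission to enrolment, so status at admission need not be status at randomisation.

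**Conclusion.** The point holds as a modest improvement. The primary model leaves out a recorded and plausibly prognostic baseline variable, and nothing in the article ties its result to the 20-point difference on which the trial was sized.

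Beyond the planned adjustment, the expected gain is about 0-16% lower variance, or 0-5 power points, with 5-8% lower variance at a conditional log odds ratio of 1.4. These figures rest on assumed prevalence and on an association assumed equal in both arms. The gain is near zero if prior use is weakly prognostic, and smaller if continued courses are not events or the algorithm stops them. In the simulated scenarios the covariate cost essentially no precision (variance ratio at most 1.01). The risk difference is worth reporting for interpretation alone.

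**What to change.** Before any outcome data are seen, the analysis plan should:

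- add antibiotic status before randomisation (yes/no) to the primary logit model, alongside severity and admission pathway. Define it from the recorded pre-admission data, with a cut-off in time that precedes randomisation and a stated rule for missing values;
- report from that model the standardised absolute risk difference with 95% CI next to the odds ratio, and name which of the two carries the primary test. The Stata software already planned can do this;
- reconcile the stratification factors, since the Intervention section lists admission route only while the Randomisation section lists severity and pathway. Until then the adjustment set itself is ambiguous.

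The cost is wording plus a coding rule for one variable. No extra patients or visits are needed, and the target of 200 should stay, because the size of the gain is unknown.
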